### Usual care

Patients are managed by a cardiologist-directed team with HF expertise. HF patient care is focused on symptom relief and use of evidence-based therapies [19, 20]. Additional goals of care include treatment of co-morbidities and patient education designed to assist with self-management techniques. For instance, we routinely target sleep disordered breathing and mood disorders, and also encourage exercise training in our HF patients as recommended by guidelines [20]. For ethical reasons, inpatient palliative care consultation at the discretion of the attending cardiologist is not denied to Usual Care patients. HF patients generally receive outpatient follow-up with an HF cardiologist focused on guideline-based medication titration, assessment of adherence to medical and dietary regimens, and serial monitoring of end-organ function. The outpatient palliative care departments of all participating centers are based not readily available to Usual Care patients. As the value of outpatient PC in the HF population is undefined, we believe it is ethically acceptable for outpatients in this arm to receive only state-of-the-art usual cardiovascular care.

### Palliative care intervention

An interdisciplinary, guideline-driven, multi-component PC intervention has been designed and administered with contemporary HF management. The goal is a structured and reproducible approach to assessing and managing the multiple domains of QoL for patients with advanced HF including physical symptoms, psychosocial concerns, spiritual concerns, and advance care planning. At the core of the palliative intervention team is a PC trained NP who coordinates this aspect of the patient’s care, a palliative care board-certified physician, and a trained counselor. Since the same cardiology team cares for patients in both the intervention and control group, the palliative care intervention is performed in collaboration with the cardiology team, but does not involve specific cardiology-based palliative interventions. This approach was designed in an attempt to minimize the extension of PC-specific interventions into the usual care study group to maintain integrity of the study design. Specific attention will be paid to assessing physical and psychosocial symptoms, establishing goals of care, assisting with decision making regarding treatment, and coordinating care on the basis of the individual needs of the patient [21].

### Physical symptoms

At study enrollment and pre-specified time points, the NP performs standardized assessments to determine the presence of commonly experienced symptoms, including dyspnea, fatigue, pain, anxiety, depression, nausea, anorexia, constipation, and insomnia. Symptoms are managed by the EPCHF palliative team using treatment algorithms to ensure standardization. In addition to periodic assessment and protocolized management of symptoms, patients in both arms are provided with an *EPCHF heart failure action plan* handout with instruction on regular control of signs that HF is getting worse and what to do if these changes occur. The handout includes information on self-management of symptoms associated with congestion and on medications typically used for HF on “as needed” basis for symptom relief at home, such as loop diuretics, and sublingual nitroglycerin [6, 22]. Patients of the interventional arm receive a handout including potential medications that may be prescribed for managing anxiety, nausea, vomiting and constipation. The medications themselves are prescribed at the discretion of the EPCHF clinical provider.

### Psychosocial symptoms

Patients are screened for symptoms of anxiety and depression using the hospital anxiety and depression scale (HADS) [23]. The HADS has been widely used in clinical trials as a psychological screening test for the states of anxiety and depression [24]. Patients screened positive for either anxiety or depression receive more thorough assessment and management as specified by a treatment algorithm used to determine the need for a mental health referral and the possible use of antidepressants, anxiolytics, stress management techniques, and psychotherapy.

### Spiritual concerns

The EPCHF NP completes a spiritual assessment at the time of patient enrollment or at the first outpatient visit after hospitalization using the FICA Spiritual History Tool [25]. FICA is an acronym which serves as a guide and includes: F—Faith and Beliefs; I—Importance in life and health; C—Community–Religious and Spiritual Community; A—How the patient would like spirituality addressed in medical care. The NP shares information gathered in the spiritual assessment with the palliative team and addresses specific spiritual concerns as appropriate. If needed, the NP arranges subsequent visits addressing concerns raised during the initial assessment.

### End-of-life preparation

To address end-of-life preparation, we use the Outlook Intervention which includes three 1-h sessions, spaced 1 week apart [26]. Session 1 focuses on life review, accomplishments, proudest moments, and cherished times. Session 2 focuses on issues of forgiveness, things the patient would have done differently, and things left unsaid or undone. Session 3 focuses on lessons learned, heritage, and legacy. To ensure replicability, the intervention follows questions outlined in the Outlook Intervention training manual. The Outlook Intervention is administered by the trained counselor.

### Goals of care

To ensure that the palliative care intervention is specified and replicable, we followed a strict fundamental protocol. Every patient randomized to palliative care was contacted every 28 days with 5-day range of tolerance. The palliative care round was structured by the themes of the modified HOPE questionnaire [27]. Patients in need for help, e.g., with applications have additional appointments by phone or in attendance. In case of symptom management e. g. pain, we contact the cardiologists or GP by phone and gave a recommendation or we involve the pain-OPD to provide prescriptions. Further palliative medical support is highly individual and depends on wishes/topics set by the patient during conversation. The intervention includes communication designed to elicit patients’ goals of care which means to determine what is most important to individuals and use those goals to frame discussions of prognosis and of life-prolonging therapies. These conversations are facilitated by the NP and revisited periodically to document changes in preferences. To ensure standardization of PC treatment, the NP was trained in a 2-day intensive workshop based on the palliative care student’s curriculum, originally designed to provide medical students with communication skills to facilitate discussions with seriously ill patients [28]. To assess this aspect of the PC intervention, we document code status, completion of advance directives, and preferences for life-prolonging therapies.

After the 12-month intervention period is completed, the NP continues to contact the patients in the intervention arm every 3 months to provide ongoing support and clinical care. In addition, the HF team is available for phone consultation to patients randomized to the intervention arm throughout the duration of the trial.

### Measurements

The primary end point is evaluated by health-related quality-of-life questionnaires after 12 months of treatment (Fig. 3). First, the functional assessment of chronic illness therapy palliative care (FACIT-Pal) score evaluating QoL living with a chronic disease and second the Kansas City Cardiomyopathy Questionnaire (KCCQ) measuring QoL living with heart failure will be determined. The FACIT-Pal is a 14-item measure of self-reported QoL that assesses several domains including physical wellbeing, social/family well-being, emotional well-being, and functional well-being [29]. KCCQ is a 23-item, disease-specific questionnaire scored from 0 to 100 with higher scores representing better health status [30]. A 5-point change in the KCCQ overall summary score has been demonstrated to be the minimally detectable clinical difference [26, 28–34].

Secondary end points are changes in anxiety/depression (HADS), symptom burden score (MIDOS), spiritual well-being Functional Assessment of Chronic Illness Therapy Spiritual Well-Being Scale (FACIT-Sp), medical resource and cost assessment, and a composite of death, HF hospitalization, and quality of life.

### Measures of health care use

The evaluation of medical resources and costs is carried out using administrative data from the computer system (KAS Orbis) of the electronic medical record of the University Hospital Bonn to analyze costs and resource usage data. The amount paid for care (e. g. through compulsory or private health insurance) should be used as a primary cost estimate. In addition, sensitivity analyzes are performed using the estimated costs of care as a measure of resource use. Differences in the use of resources in the study arms are examined in order not only to determine the extent of the cost differences, but also to identify the sources that make the difference. At all visits, patients are asked if they have been treated outside the study hospital. If so, they are asked to estimate the number of visits and/or days in the hospital. The cost of such care is estimated on the basis of the medical expenditure survey and included in the total cost of care from the time of randomization until the completion of the study.

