## Abstract

The progressive nature of heart failure (HF) coupled with high mortality and poor quality-of-life (QoL) mandates greater attention to palliative care (PC) as a routine component of HF management. Limited evidence exists from randomized controlled trials supporting the use of interdisciplinary palliative care in the progressive course of HF. The early palliative care in heart failure trial (EPCHF) is a prospective, controlled, nonblinded, multicenter study of an interdisciplinary palliative care intervention in 200 patients with symptomatic HF characterized by NYHA ≥ 2. The 12-month EPCHF intervention includes monthly consultations by a palliative care team focusing on physical and psychosocial symptom relief, attention to spiritual concerns and advance care planning. The primary endpoint is evaluated by health-related QoL questionnaires after 12 months of treatment. First the functional assessment of chronic illness therapy palliative care (FACIT-Pal) score evaluating QoL living with a chronic disease and second the Kansas City cardiomyopathy questionnaire (KCCQ) measuring QoL living with heart failure will be determined. Secondary endpoints are changes in anxiety/depression (HADS), symptom burden score (MIDOS), spiritual well-being functional assessment of chronic illness therapy spiritual well-being scale (FACIT-Sp), medical resource and cost assessment. EPCHF will help evaluate the efficacy and cost-effectiveness of palliative care in symptomatic HF using a patient-centered outcome as well as clinical and economic endpoints. EPCHF is funded by the Bundesministerium für Bildung und Forschung (BMBF, 01GY17).

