## Summary

HF creates significant physical, psychosocial and spiritual burden for patients and their families. Palliative care may represent an important component of the holistic management of patients with not only advanced HF. Further evidence from randomized trials of a palliative care intervention in HF is required to identify which patients may benefit from specific interventions. EPCHF aims to provide empiric data to support the efficacy and cost-effectiveness of palliative care improving the health-related QoL in HF patients after hospitalization. Such evidence could provide impetus to overcome current challenges related to limited access to, and adoption of, palliative care services for HF patients.

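### The payment-based primary cost estimate gives no value to palliative care contacts that generate no payment, so the cost difference can be biased in favour of the intervention

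*Protocol article*

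**What the plan says.** All references are to the protocol article.

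- **Primary cost measure** (Measures of health care use): "The amount paid for care (e. g. through compulsory or private health insurance) should be used as a primary cost estimate".
- **Data source** (same section): costs and resource use are analysed "using administrative data from the computer system (KAS Orbis) of the electronic medical record of the University Hospital Bonn".
- **Sensitivity analysis** (same section): "In addition, sensitivity analyzes are performed using the estimated costs of care as a measure of resource use". The section also plans to look for the sources of any cost difference.
- **Care elsewhere** (same section): patients report treatment received outside the study hospital. "The cost of such care is estimated on the basis of the medical expenditure survey and included in the total cost of care".
- **Programme contacts** (Goals of care): "Every patient randomized to palliative care was contacted every 28 days with 5-day range of tolerance". That section adds further appointments by phone or in person where needed, and nurse contacts every 3 months after month 12.
- **Counsellor sessions** (End-of-life preparation): "three 1-h sessions, spaced 1 week apart".
- **Control arm** (Fig. 1 legend and Usual care): palliative care is given only on demand, and the outpatient palliative service is not readily open to these patients.
- **Funding and aim**: "EPCHF is funded by the Bundesministerium für Bildung und Forschung" (Abstract), and "EPCHF aims to provide empiric data to support the efficacy and cost-effectiveness of palliative care" (Summary). Measurements lists cost among the secondary endpoints.

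**The concern.** The palliative care programme is the one resource that differs between the arms by design. A payment-based measure values a service only if somebody's payment for it is recorded. Some of the programme is of a kind that may leave no such record: phone appointments, advice calls to cardiologists or general practitioners, counsellor sessions and nurse follow-up calls.

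If those contacts enter at zero, the programme's cost is missing from the intervention arm, while any hospital days it saves are still credited in full. The controls have no scheduled programme, so nothing offsets the omission. The error can run in one direction only. A programme that is cost-neutral or more costly could then appear cost-saving, in a trial that names cost-effectiveness as an aim.

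**Working it through.** The article states no cost figure, so there is nothing to reproduce. The check is which costs the stated rule admits, and how large the gap could be.

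**Step 1. What enters the primary total under the stated rule**

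| Resource | Route into the total | Arm affected |
|---|---|---|
| Care at the study hospital with a recorded payment | Amount paid | Both |
| Care outside the study hospital | Estimated cost added | Both |
| Programme contact with a recorded payment | Amount paid | Intervention |
| Programme contact without a recorded payment | None stated | Intervention |

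The section does supplement payments where it recognises that hospital data miss something (care elsewhere). It makes no such addition for the programme.

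**Step 2. Number of scheduled contacts per intervention patient in year 1**

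- One contact every 28 days: 365 / 28 = 13.04, so 13. If contacts are monthly (Trial design): 12.
- Outlook sessions, where delivered: 3.
- Lower count, monthly contacts without Outlook sessions: 12. Upper count: 13 + 3 = 16.
- Arm size, from 200 patients allocated 1:1: 200 / 2 = 100. Contacts in the arm if all complete: 12 × 100 = 1,200 to 16 × 100 = 1,600.
- Statistical analysis expects about 20% drop-out, mainly from death. If all of it fell at time zero, the lower count would be 1,200 × 0.8 = 960.

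**Step 3. After month 12**

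Fig. 2 gives 38 months from first patient in to last patient out and 26 months of recruitment.

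- The first recruits have 38 − 12 = 26 months left. 26 / 3 = 8.7, so 8 completed quarterly contacts.
- The last recruits have 38 − 26 − 12 = 0 months left, so none.
- With even recruitment the average is about 13 months, and 13 / 3 = 4.3, so about 4 contacts.

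**Step 4. Size of the omission**

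Let n be contacts per patient, b the share with a recorded payment, and u the cost of a contact. Then

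omission per intervention patient = n × (1 − b) × u.

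- b = 1: omission = 0.
- b = 0: omission = n × u, the full cost of 12 to 16 contacts in year 1.

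The article gives neither b nor u. For scale only, with b = 0 and assumed values of u:

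| Assumed u (EUR) | 12 × u | 16 × u |
|---|---|---|
| 25 | 300 | 400 |
| 50 | 600 | 800 |
| 100 | 1,200 | 1,600 |
| 150 | 1,800 | 2,400 |

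These are upper bounds for each u, because they assume full completion and no billing.

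**The case against.** A reader might infer that the primary measure counts insurer payments only, that the grant pays for the programme, and that the cost comparison is therefore tilted. The article does not support this. Insurance is introduced as an example, so other payers are not excluded. The total also includes estimated costs of care elsewhere, so it is not a pure insurer figure. The article says the trial is grant-funded, but not that the grant pays for the contacts or that they go unbilled. Hospital palliative care departments deliver them, partly during inpatient stays, and some or all may generate ordinary payments. This part of the objection stands and makes the bias conditional.

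Four further points deserve weight.

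- **The sensitivity analysis could capture unbilled contacts.** True, and nothing says it leaves them out. But it does not name the programme, and it leaves the primary estimate as it is.
- **Costing details may sit in the full protocol or analysis plan.** Unit costs and valuation rules may well be there. The point here concerns the rule that the article itself states, under which a service without a payment has no value.
- **A payer perspective is a legitimate choice.** It is. But a comparison that can leave out the programme's own cost is weak support for a claim about the programme's cost-effectiveness.
- **Cost is a secondary endpoint, and secondary endpoints are analysed descriptively.** That limits the consequence. No primary quality-of-life conclusion is affected.

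The size is also uncertain. The unit costs are assumed, the contact counts are upper bounds, and no total cost or variance is available to show whether a conclusion would reverse.

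**Conclusion.** The point holds in conditional form. Under the stated rule, any programme contact without a payment record enters the primary cost estimate at zero, in the intervention arm only. The direction of the resulting error is known: the cost difference, intervention minus control, would be too low. Its size is not known. It runs from zero, if every contact is billed, to the full cost of about 12 to 16 scheduled contacts per patient in year 1, fewer with drop-out. Extra appointments and the quarterly contacts after month 12 would add to it. Any euro figure rests on an assumed unit cost. The change is worth making because cost-effectiveness is a stated aim, and because the correction does no harm if all contacts turn out to be billed.

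**What to change.** In Measures of health care use, define the primary cost estimate as the amount paid for care plus the cost of delivering the EPCHF intervention, at both centres. Count the 28-day contacts, Outlook sessions, additional appointments and quarterly contacts. Value those not already billed as number of contacts × staff time × wage rate, and leave billed contacts at the amount paid to avoid double counting. Report the payment-only figure as a sensitivity analysis. If all contacts are billed, the two figures coincide.

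The cost is a sentence in the plan, a small unit-cost table and a count of contacts from the intervention records. The article does not describe a log of contacts or staff time, so the sponsor should confirm that such records exist; standard times per contact type could stand in for measured staff time. No patient procedure changes. The downside is that the cost difference may look less favourable to the intervention.

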### Data collection

Participants complete baseline questionnaires before randomization. A complete schedule of assessments is given in Fig. 3. Follow-up evaluations of QoL and mood are expected to occur at 3 months, 6 months, 9 months and 12 months. As necessary, we will mail questionnaires to subjects and/or complete questionnaires over the telephone to help ensure the collection of primary endpoint data. When responses on questionnaires were incomplete, research staff documented the reasons for which the participant did not give a full response.

### Statistical analysis

Primary endpoints: the two primary endpoints will be tested in a two-step procedure. In the first step the hypothesis of equal scores for the FACIT-Pal in the two treatment groups will be tested with a two-side *t* test at a level of 5%. In case of the rejection of the null-hypothesis in the first step, the second hypothesis of equal KCCQ-scores in the two treatment groups will be tested again with a two-sided *t* test at the level of 5%. This test procedure controls a family wise error rate of 5%.

A comparably high number of drop-outs (~ 20%) especially due deaths are to be expected. Since this kind of censoring is definitely correlated to the QoL-measurement, the results for the QoL-score might be biased. An optimal choice of a procedure for the replacement of missing values would require a detailed knowledge about this correlation, which is not available. Missing values will not be replaced for the primary analysis of the two primary outcome variables. A sensitivity analysis will be performed replacing missing values by the last observation carried forward method.

For both variables the course of QoL scores over the observational time will analyzed descriptively by fitting mixed linear models to the data. 95%-confidence interval will be estimated for the score values separated by treatment groups and for measurement times. A second identical analysis for the primary endpoint will be performed based on the per-protocol population (PP), which is defined as the patients treated and observed according to protocol. This analysis will only be performed if ITT and PP-population differ.

Secondary endpoints: the secondary endpoints will be analyzed descriptively in the intention-to-treat collective.

Psychosocial symptoms: patients are screened for symptoms of anxiety and depression using the Hospital Anxiety and Depression Scale (HADS). The HADS has been widely used in studies as a psychologic screening test for the states of anxiety and depression. Patients who screen positive for either anxiety or depression receive a more thorough assessment and management as specified by a treatment algorithm used to determine the need for a mental health referral and the possible use of antidepressants, anxiolytics, stress management techniques, and psychotherapy.

Spiritual concerns: the EPCHF-HF NP completes a spiritual assessment at the time of patient enrolment or at the first outpatient visit after hospitalization using the FACIT-Sp. The NP shares information gathered in the spiritual assessment with the EPCHF team and addresses specific spiritual concerns as appropriate. If needed, the NP arranges for subsequent visits to address concerns raised during the initial assessment.

Moreover, qualitative interview data will supplement the results of questionnaires and gain information about the impact of gender issues and social inequality (e.g., patients with migrant background within the study). In addition, public health researcher with special expertise in the area of health inequality research will analyze the issue between over-indebtedness and HF. Because of the expected relevance of variables pertaining to socioeconomic status and migration background for HF-related outcomes including psychosocial aspects/issues, a careful evaluation of the associations between primary and secondary endpoints and these variables will be investigated.

The secondary endpoints HADS-D, MIDO, FACIT-Sp will be analyzed for differences between the treatment groups by fitting mixed linear models to the data. 95%-confidence interval will be estimated for the score values separated by treatment groups and for measurement times.

The survival times will be compared between the treatment groups by a log-rank test. Cox-proportional hazard models will be used to further explore the impact of the treatment on the survival of the patients.

The frequency of adverse events will be counted in absolute and relative frequencies, separated by treatment groups and depending on severity and relationship to the therapy.

Further details of the analyses for primary and secondary outcomes will be specified in a statistical analysis plan.

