## Methods

### Trial design

EPCHF is a prospective, controlled, two-arm, non-blinded, randomized, multicenter clinical trial of early palliative care integrated with standard cardiac care, as compared with standard cardiac care alone (Fig. 1). The multicenter study will be performed at the departments of Internal Medicine and Palliative Care of the University Hospital of Bonn and departments of Internal Medicine and Palliative Care of the University Hospital of Düsseldorf. Eligible patients with symptomatic HF and dyspnea NYHA ≥ 2 will be randomly assigned to one of the two groups in a 1:1 ratio to usual contemporary HF care or usual care combined with the EPCHF intervention (Fig. 1). Subjects are assigned treatment using a complete randomization scheme. Patients who are assigned to early PC will meet with a member of the PC team, which consisted of board-certified PC physicians and advanced-practice nurses within the time of hospitalization after enrollment and at least monthly thereafter in the outpatient setting during the 12 months of follow-up (Figs. 2 and 3). The palliative care intervention focuses on symptom relief, attention to spiritual concerns, and advance care planning. The trial is non-blinded, since it is not possible to execute a double-blinded trial of the EPCHF intervention given that the intervention involves a multidisciplinary team. The duration of the intervention is 12 months, but patients in both groups are followed until death or the end of the study (~ 3.5 years). The primary endpoint refers to health-related QoL after 12-month follow-up (Fig. 3).

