### Study population

The study will enroll patients with symptomatic HF defined by dyspnea NYHA ≥ 2. Inclusion and exclusion criteria are presented in Tables 1 and 2. Mortality risk due to HF will be calculated by the Seattle Heart Failure Score [18].

**Table 1 Tab1:** Inclusion criteria

Inclusion criteria	Subjects will only be included in the study if they meet all of the following criteria
	Age ≥ 18 years
	NYHA class II–IV symptoms (suspected cardiac dyspnea)
	Systolic HF with a LVEF ≤ 35% or HF with preserved ejection fraction (NYHA class II–IV, elevated natriuretic peptides (NP), left ventricular hypertrophy (LVH) or left atrial enlargement (LAE) or diastolic dysfunction
	BNP ≥ 100 pg/mL or NT proBNP ≥ 400 pg/mL
	Subjects with the ability to follow study instructions and likely to attend and complete all required visits
	Written informed consent

**Table 2 Tab2:** Exclusion criteria

Exclusion criteria	Subjects will not be included in the study if any of the following criteria applies
	Inability to read, understand and respond to question in German
	Previous consultations of palliative care services
	Patients in intensive care unit, on a ventilator, pre- or post-heart transplant
	Non-cardiac terminal illness
	Women who are pregnant or planning to become pregnant, nursing women
	Simultaneously participation in another study or participation in any study involving administration of an investigational medicinal product within 30 days prior to study beginning
	Subjects with a physical or psychiatric condition which at the investigator’s discretion may put the subject at risk, may confound the trial results, or may interfere with the subject’s participation in the study
	Known or persistent abuser of medication, drugs or alcohol

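### Free improvement: both primary t tests leave out baseline scores collected before randomisation; adjusting for them would gain precision and remove the effect of chance baseline differences

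*Protocol article*

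**What the plan says.** The Abstract describes a "multicenter study of an interdisciplinary palliative care intervention in 200 patients with symptomatic HF". Under Trial design, patients "will be randomly assigned to one of the two groups in a 1:1 ratio to usual contemporary HF care" or to usual care plus the intervention, and "Subjects are assigned treatment using a complete randomization scheme". No strata or blocks are named. The same section places the primary endpoint at 12 months.

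Under Statistical analysis, both confirmatory tests are t tests at 5%. For FACIT-Pal the text reads: "In the first step the hypothesis of equal scores for the FACIT-Pal in the two treatment groups will be tested with a two-side". KCCQ follows only if that null hypothesis is rejected: "the second hypothesis of equal KCCQ-scores in the two treatment groups will be tested again with a two-sided". The section concludes: "This test procedure controls a family wise error rate of 5"%.

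Missing values are not replaced in the primary analysis, and drop-out of about 20% is expected, largely from deaths. The sensitivity analysis changes only the handling of missing values, the per-protocol analysis is otherwise identical, and the mixed linear models for the two primary scores are described as descriptive.

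Under Data collection: "Participants complete baseline questionnaires before randomization".

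**The concern.** The baseline score of the same questionnaire is measured free of any influence of treatment and is already in the data set. A two-sample t test cannot use it. If baseline and 12-month scores are correlated, two things follow:

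- The confidence interval for each primary endpoint is wider than it needs to be.
- If one arm happens to start with better quality of life, part of that head start appears in the 12-month difference.

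The population spans two centres, NYHA II to IV, and both reduced and preserved ejection fraction, and no stratification is described. The fixed sequence raises the stakes, because missing significance on FACIT-Pal means KCCQ is not tested at all.

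This is not a detail left to the analysis plan. The article defers further details, but it has already named the test.

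**Working it through.** **Inputs from the article.** 200 patients (Abstract); 1:1 allocation (Trial design); two-sided 5% and about 20% drop-out (Statistical analysis).

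**Assumptions.** Drop-out is equal in both arms. The correlation ρ between baseline and 12-month score lies between 0.3 and 0.7. The article gives no value for ρ.

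**The plan's own figure.** The sample size of 200 cannot be reproduced, because no target effect, SD or power is stated with it.

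**1. Evaluable patients.** 200 × (1 − 0.20) = 160, or 80 per arm.

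**2. Detectable difference of the t test at 80% power.** Normal approximation: (1.960 + 0.842) × √(2/80) = 2.802 × 0.158 = 0.443 SD. The exact noncentral t calculation gives 0.446 SD. With all 200 patients the approximation gives 2.802 × √(2/100) = 0.396 SD.

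**3. The same under ANCOVA.** Residual variance falls by the factor 1 − ρ², so the detectable difference is 0.446 × √(1 − ρ²). The equivalent number of unadjusted completers is 160 / (1 − ρ²).

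| ρ (assumed) | 1 − ρ² | Detectable difference (SD) | Equivalent completers | Gain |
|---|---|---|---|---|
| 0 (t test) | 1.00 | 0.446 | 160 | – |
| 0.3 | 0.91 | 0.425 | 176 | 10% |
| 0.4 | 0.84 | 0.408 | 190 | 19% |
| 0.5 | 0.75 | 0.386 | 213 | 33% |
| 0.6 | 0.64 | 0.357 | 250 | 56% |
| 0.7 | 0.51 | 0.318 | 314 | 96% |

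The extra degree of freedom spent on the covariate does not change these figures at three decimals.

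**4. Power at an illustrative effect.** At an assumed true difference of 0.40 SD (not a figure from the article), power is 71% unadjusted. Adjusted, it is 75%, 83% or 94% for ρ = 0.3, 0.5 or 0.7.

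**5. Chance baseline differences.** With 80 per arm, the baseline difference in means has SD √(2/80) = 0.158 SD units. It exceeds 0.2 SD in either direction in 21% of randomisations and 0.3 SD in 5.8%.

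**6. What a realised difference does to the t test.** Given a baseline difference d and no treatment effect, the test statistic is approximately normal with mean ρd/0.158 and SD √(1 − ρ²). For d = 0.3 and ρ = 0.5, the mean is 0.15/0.158 = 0.949 and the SD 0.866. The upper tail is P(Z > (1.960 − 0.949)/0.866) = P(Z > 1.17) = 12.2%, and the lower tail is negligible. The conditional false-positive rate is therefore 7.6%, 12.2% or 18.8% for ρ = 0.3, 0.5 or 0.7. At d = 0.2 it is 5.6%, 6.4% or 6.6%. Averaged over all randomisations it is 5%.

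**The case against.** The strongest reply is that nothing here is an error. In a 1:1 randomised trial the unadjusted t test is valid: its standard error already includes chance baseline variation, and its level over randomisations is 5%. That stands. A reader might infer that the plan has no protection against imbalance, or that its result would be biased. The article does not support that. What remains is lost precision, and bias conditional on the allocation that happens to occur.

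Second, the gain depends on a correlation the article does not give. That also stands. Over 12 months of progressive disease, and among completers only, it could be modest. At 0.3 the gain is 10%, and 96% is only the top of the range.

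Third, the mixed models give estimates by arm and measurement time, and baseline is one of the data-collection times, so an imbalance could be seen there. True, but those models are descriptive and leave the confirmatory tests unchanged.

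Two further inferences should not be drawn. One is that complete randomisation threatens a badly uneven split within a centre. The article gives no enrolment by centre, and an uneven split concerns arm size, not baseline quality of life. A 60:40 split would keep 4 × 0.6 × 0.4 = 96% of the information. The other is that the survival model wrongly omits the Seattle Heart Failure Score. The covariates of the Cox models are left open, so there is no stated choice to correct.

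**Conclusion.** The point holds as a free improvement, not as a defect that invalidates the primary analysis. It is certain that the article names unadjusted tests for both primary endpoints while the baseline scores are collected before randomisation. The size of the loss is less certain. With about 80 completers per arm, adjustment is worth between about 10% and 96% more completers for correlations from 0.3 to 0.7, with 33% at 0.5. Any non-zero correlation of practical size gives a gain in the same direction. A gain on FACIT-Pal also helps to keep the KCCQ test open.

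That randomisation is unstratified is inferred from the term used and from the absence of named strata; the article does not say so outright. Equal drop-out by arm is assumed throughout.

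**What to change.** Replace both t tests by ANCOVA of the 12-month score on treatment, with the baseline score of the same instrument and centre as prespecified covariates. Keep the order FACIT-Pal then KCCQ, each at two-sided 5%. Retain the t tests as a sensitivity analysis.

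No new data, visits or patients are needed. The cost is procedural: a published confirmatory test is being changed in a non-blinded trial. The change therefore needs a dated, documented amendment, reflected in the analysis plan, before anyone examines outcome data by arm. Covariates added later would not be credible.

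Baseline adjustment does not by itself resolve the bias from deaths and drop-out that the Statistical analysis section acknowledges. That needs separate treatment.
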